#### Exploratory analysis {20b}

Subgroup analyses based on patients’ clinical characteristics will be performed in pre-specified post hoc exploratory analyses. Potential factors impacting the examination success rate include BMI, age, the presence of respiratory diseases, cardiovascular and cerebrovascular diseases, liver and kidney dysfunction, alcohol and drug dependence, and operator experience.

Repeated measurement data (e.g., multiple measurements of MOAA/S, NIBP, HR, and SpO_2_) will be analyzed using a generalized additive mixed model (GAMM). The fixed effect will be a stratification indicator (invasive procedures during upper gastrointestinal endoscopy and treatment), and the interaction between groups and time will be evaluated.

#### Sensitivity analysis {20c}

Broaden the primary outcome measure’s success criteria to fulfill the following two conditions: (1) MOAA/S ≤ 3 points before endoscope insertion into the oral cavity and (2) no interruption due to sedation during upper gastrointestinal endoscopy and treatment. Reassess the difference in success rates between the two patient groups. B. Utilize a per-protocol (PP, only includes participants who adhered to the study protocol and completed the entire study) analysis to select specific patients for effect estimation.

Analysis population and missing data: A multiple-imputation analysis will be performed to further evaluate whether the use of indicator variables for missing data introduces bias into our results.

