### Interventions {11a}

Upon obtaining signed informed consent from the subject, the following process is executed (Figs. 2 and 3):Screening periodAfter the patient enters the endoscopy examination room and decides to undergo upper gastrointestinal endoscopy treatment, the researcher collects information on the patient’s demographics, medical condition, and proposed examination plan. An independent anesthesiologist evaluates the patient’s examination plan before randomization, and eligible patients are selected based on the inclusion/exclusion criteria. Patients should be assessed by researchers who are knowledgeable about the protocol and authorized to do so in a quiet environment. The study’s purpose, methods, potential benefits, and risks must be thoroughly explained to the patient and/or their representative, and data collection and follow-up procedures before, during, and after the examination must be detailed.The researchers should address the patient and their family members’ questions in detail, allowing sufficient time for consideration and obtaining informed consent from the patient and/or their representative on a completely voluntary basis. The assessor must not be involved in the patient’s examination, sedation, or anesthesia management plan. *Sedation management plan*: An anesthetist with the title of attending physician or above will implement the sedation and anesthesia plan. The patient enters the endoscopy consultation room’s preparation area and takes 10 g of lidocaine gel (containing 0.2 g of lidocaine) orally 5 min before the examination. The patient assumes a left lateral position on the treatment bed in the endoscopy consultation room, and basic vital signs including noninvasive blood pressure (NIBP) of the right upper arm, electrocardiogram, and pulse oxygen saturation (SpO_2_) are monitored. Oxygen is continuously administered through a 4L/min nasal cannula throughout the procedure until the patient fully awakens. A venous line is established, and sufentanil 5 μg is administered intravenously. Patients scheduled for upper gastrointestinal endoscopy are randomized to receive one of two sedative drug infusions: propofol in group C or remimazolam in group R. In group C, patients receive a single dose of propofol at 1.5 mg/kg, while in group R, patients receive a single dose of remimazolam at 0.15 mg/kg, both administered within 1 min. According to the domestic expert consensus, moderate or deep sedation is required for upper gastrointestinal endoscopic examination. Therefore, the MOAA/S score (Appendix 2) should be assessed 1 min after propofol injection. If the MOAA/S score is greater than 3 points, propofol 0.5 mg/kg or remimazolam 0.05 mg/kg should be administered repeatedly until the MOAA/S score is less than or equal to 3 points, with a maximum of five repetitions. The VAS (Appendix 3) should be assessed during propofol or remimazolam injection.*Intraoperative monitoring*: Intraoperative monitoring includes electrocardiogram, noninvasive blood pressure, pulse oxygen saturation, and, when necessary, body temperature, urine output, end-tidal carbon dioxide concentration, and blood glucose levels.*Sedation maintenance plan*: During the examination procedure, the chief anesthesiologist determines whether to administer additional trial medication based on the surgical process and duration. Propofol (0.5 mg/kg) or remimazolam (0.05 mg/kg) is administered in single doses with a minimum interval of 1 min to maintain the patient at an appropriate level of sedation (MOAA/S score ≤ 3). If sedatives are insufficient to maintain appropriate sedation during the examination, the investigator may decide to use alternative sedative agents (midazolam).*Examination plan*: Based on the type of lesion, the endoscopic examination of the upper digestive tract in our hospital may include, but is not limited to, upper gastrointestinal inflammation, tumors, ulcers, polyps, gastroesophageal varices, and gastrointestinal strictures. According to the type of endoscopic treatment of the upper gastrointestinal tract, it may include, but is not limited to, sclerotherapy, argon plasma coagulation, high-frequency electrocautery, and submucosal dissection. Various procedures are conducted following established clinical surgical protocols. *Postoperative management plan*: After the examination or procedure, the patient enters the anesthesia recovery room, where continuous monitoring of ECG, noninvasive blood pressure, and oxygen saturation occurs. The MOAA/S score is assessed every 5 min. Once the score reaches 5 points for three consecutive assessments, and blood pressure, heart rate, and oxygen saturation are normal and stable, the patient can leave the recovery room accompanied by a companion. In case of special circumstances, refer to the adverse event handling procedures.

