### Criteria for discontinuation or modification of allocated interventions{11b}

We do not plan to intentionally alter the specified interventions. However, it should be emphasized that participation in all the interventions detailed in the program is at the discretion of the individual participants. They have the freedom to choose whether to engage in or omit any of the intervention measures. Thus, if participants perceive any aspect of the intervention as less beneficial, they may opt out of that component.

The attending anesthesiologist has the authority to discontinue a participant’s involvement in the trial at any point for medical reasons. This responsibility, including the assessment of factors such as adverse reactions, lies solely with the attending anesthesiologist. Furthermore, participants have the right to withdraw from the study whenever they wish by revoking their consent.

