### Sample-size calculation {14}

The study plans to enroll 576 patients. The basis for sample size calculation is as follows: According to the literature report [7], patients undergoing upper gastrointestinal endoscopy and treatment with propofol sedation had a completion rate without sedation-related complications of 79%. Using a two-sample *z*-test for proportions to assess the primary outcome measure, the estimated non-inferiority margin is an absolute difference of 10% for the primary outcome measure. Setting a non-inferiority difference value of 0.1, a power (1-β) of 0.8, and a one-sided α of 0.025, a total sample size of 522 cases is required for the calculation. Accounting for an anticipated loss to follow-up rate of 10%, the total sample size is 576 cases (288 participants per group).

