#### Efficacy evaluation{20a}

Primary endpoint evaluation: In the intention-to-treat (ITT) analysis population, a chi-square test will be used to compare the success rates of patients completing endoscopic examination and treatment between the two groups. Simultaneously, a generalized linear model will be employed to calculate the unadjusted and adjusted absolute risk differences (ARD). Adjusted variables will encompass stratification indicators (invasive procedures during upper gastrointestinal endoscopy and treatment), BMI, age, concurrent respiratory diseases, concurrent cardiovascular and cerebrovascular diseases, liver and kidney function abnormalities, and operator experience. Secondary effect sizes will be presented as odds ratios (OR) with a 95% confidence interval.

Evaluation of secondary endpoints: For the intention to treat (ITT, includes all participants who were randomly assigned, regardless of whether they completed the entire study or fully adhered to the study protocol) population, chi-square test or *t*-test will be employed for comparative analysis based on variable nature (e.g., categorical variables like low oxygen saturation, hypotension, tachycardia, intraoperative awareness, recovery delay, or continuous variables such as MOAA/S, NIBP, HR, and SpO_2_). Results will be reported as odds ratios (OR) and 95% confidence intervals using a generalized linear model. Time event variables (e.g., time to achieve a MOAA/S score of ≤ 3 points after a single dose) will be analyzed using Cox regression to describe and compare the two groups, generate Kaplan-Meier curves, express results as hazard ratios (HR), and report a 95% confidence interval.

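### The per-protocol set is limited to participants who completed the study, so it can drop primary-endpoint failures and is an unreliable check on the ITT non-inferiority result

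*Protocol article*

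**What the plan says.** All references are to the protocol article.

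- **Primary analysis (Efficacy evaluation {20a}).** "In the intention-to-treat (ITT) analysis population, a chi-square test will be used to compare the success rates". The same section defines ITT as everyone randomised, whatever their completion or adherence.
- **Per-protocol analysis (Sensitivity analysis {20c}, item B).** "Utilize a per-protocol (PP, only includes participants who adhered to the study protocol and completed the entire study) analysis". It is supportive; no text gives it a part in the non-inferiority decision.
- **Primary outcome.** Success needs all four criteria. One is that the examination was not interrupted for inadequate sedation. Two others rule out low oxygen saturation and out-of-range systolic pressure or heart rate.
- **Discontinuation {11b}.** "The attending anesthesiologist has the authority to discontinue a participant" for medical reasons, with adverse reactions named among the factors to be assessed.
- **Blinding {17a}.** Those giving the intervention know the allocation and also assess outcome.
- **Follow-up.** There is one contact, by telephone, on the day after the procedure.

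**The concern.** A per-protocol analysis in a non-inferiority trial is there to show whether departures from protocol have hidden a real difference. It can do that only if membership of the set does not depend on the outcome.

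Here the definition has two conditions, adherence and completion, and the second overlaps with the endpoint. A patient whose endoscopy is stopped for inadequate sedation, or who is taken out for hypoxia or hypotension, is a primary-endpoint failure and may also count as not having completed. The person with authority to discontinue knows which drug was given. If such patients leave the set, its success rates are raised in whichever arm they leave. Agreement between the per-protocol and ITT results would then reassure less than it appears to, and disagreement would be hard to interpret.

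**Working it through.** **1. Inputs (Sample-size calculation {14}).** Propofol patients "had a completion rate without sedation-related complications of 79"%. For the margin, "the estimated non-inferiority margin is an absolute difference of 10% for the primary outcome measure". The error rates are "a power (1-β) of 0.8, and a one-sided α of 0.025". Planned arms are 288 each.

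**2. The plan's own figure.** With both arms at 79% (equality is not stated, but it reproduces the total):

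n per arm = (1.960 + 0.842)² × 2 × 0.79 × 0.21 / 0.10² = 260.4, rounded up to 261, so 522 in total. This matches "a total sample size of 522 cases is required for the calculation". Then 261 × 1.1 = 287.1, rounded up to 288 per arm, or 576. The sample size is not in dispute.

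**3. Set the truth at the margin.** Propofol 79%, remimazolam 69%. An unbiased analysis then declares non-inferiority wrongly 2.5% of the time.

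**4. Remove a fraction f of failures from each arm (f is assumed).**

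- success rate left: p′ = p / (p + (1 − p)(1 − f))
- arm size left: n′ = 288 × (1 − (1 − p)f)
- SE = √(p′C(1 − p′C)/n′C + p′R(1 − p′R)/n′R), with C = propofol and R = remimazolam
- probability of declaring non-inferiority = Φ((0.10 − deficit)/SE − 1.96)

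| f | Propofol p′ (n′) | Remimazolam p′ (n′) | Apparent deficit | One-sided error |
|---|---|---|---|---|
| 0 | 79.0% (288) | 69.0% (288) | 10.0 points | 2.5% |
| 10% | 80.7% (282) | 71.2% (279) | 9.5 points | 3.5% |
| 20% | 82.5% (276) | 73.6% (270) | 8.9 points | 5.0% |
| one third | 85.0% (268) | 77.0% (258) | 8.0 points | 8.5% |

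The arm sizes fall with the exclusions. Keeping 288 per arm in the SE would give about 9% in the last row.

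**5. Remove failures from one arm only.** Here x is the share of that arm's patients removed, all of them failures: p′ = p/(1 − x), n′ = 288(1 − x).

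| Arm losing failures | x | Apparent deficit | One-sided error |
|---|---|---|---|
| Remimazolam | 2% | 8.6 points | 5.8% |
| Remimazolam | 5% | 6.4 points | 17.0% |
| Propofol | 2% | 11.6 points | 0.8% |
| Propofol | 5% | 14.2 points | 0.1% |

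Equal fractional loss pulls the difference towards zero. One-sided loss moves it either way, depending on the arm.

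**The case against.** **The wording may not mean that.** Completing the entire study could mean reaching the day-1 telephone contact. An interruption is a recorded event and need not end participation. Many failures, such as a brief desaturation or a heart rate out of range, occur in patients who finish both the procedure and follow-up. This stands as a limit on size: the text does not say how many failures would be lost. It does not remove the point, because the meaning is left open in the definition the protocol itself states, and unblinded staff decide on discontinuation.

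**The direction is unknown.** The Background and Discussion attribute respiratory depression and hypotension to propofol. Removals for adverse reactions could therefore fall mainly on that arm and make the per-protocol analysis conservative. This stands in full.

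**Exact membership belongs in an analysis plan.** Often so, and that plan is not shown. But the article states a rule, and completion is part of it.

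**A stronger reading does not follow.** A reader might infer that resting the decision on ITT is itself an error that inflates false non-inferiority, because "the investigator may decide to use alternative sedative agents (midazolam") in either arm and patients may omit parts of the intervention. The documents do not support this. Midazolam is permitted by the protocol, so its use is not non-adherence, and a per-protocol set defined by adherence would keep those patients too. Dilution counts as error only against an effect under full adherence, and the protocol names no such target. ITT as primary with a supportive per-protocol analysis is an accepted approach.

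**Conclusion.** The point holds for the definition of the per-protocol set and no further. As written, the completion condition can exclude patients because they failed the primary endpoint, so the analysis is an unreliable check on the ITT result.

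The size is illustrative. Under equal fractional loss of 10% to one third of failures, a true 10-point deficit appears as 9.5 to 8.0 points, and the one-sided error is about 3.5% to 8.5% instead of 2.5%. Under loss from propofol alone it falls below 2.5%. These figures assume true rates of 79% and 69%, a normal approximation and exclusion fractions that the documents do not supply. They describe the sensitivity analysis; they do not show that the ITT test is biased.

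A reader might also infer that non-inferiority must be shown in both sets. The protocol does not require this, and it would be a trade-off, not a correction. With 79% in both arms, ITT alone at 288 per arm has 83.8% power. If 10% are excluded (259 per arm), the per-protocol set has 79.8% and the chance that both succeed is about 78%, under the planned 80%.

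**What to change.** Change the definition in Sensitivity analysis {20c}:

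1. Define the per-protocol set by eligibility, receipt of the allocated drug at induction, and absence of major deviations unrelated to outcome. Drop the condition on completing the study.
2. State that patients with an interrupted examination, respiratory or circulatory instability, or discontinuation for an adverse reaction remain in the set and count as failures.
3. Report the per-protocol risk difference with its two-sided 95% confidence interval against the -10 point margin, beside the ITT result, and discuss any discordance.

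The cost is a change of wording: the analysis is already planned, and no patients or procedures are added. The downside is that the new set will lie closer to ITT and so differ from it less. Requiring success in both sets is optional and not part of this change.

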### Randomization and allocation concealment {16}

The randomization method employs variable block randomization with random-sized blocks. Professional statisticians not involved in data management utilize the Data Web data collection management system to generate a central random sequence, randomly allocating subjects in a 1:1 ratio and dividing them into two groups. Stratification is based on whether upper gastrointestinal endoscopic invasive treatment is planned, as this factor may influence the duration of the procedure and potentially affect the sedation success rate. Random numbers are placed in coded, opaque envelopes and entrusted to personnel not involved in anesthesia or data collection for management.

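### Patients without a usable outcome are dropped despite an all-randomised ITT, and the stated missing-data check cannot show whether non-inferiority survives this

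*Protocol article*

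**What the plan says.** Under Sensitivity analysis {20c}, one sentence of the protocol article deals with missing data. A multiple imputation will assess "whether the use of indicator variables for missing data introduces bias into our results". Indicators are thus the working method and imputation is a check on them. No variable is named. The same section lists a broadened success definition and a per-protocol analysis limited to adherent completers.

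Efficacy evaluation {20a} places the primary comparison in the ITT population. In its paragraph on secondary endpoints it defines ITT as the set that "includes all participants who were randomly assigned, regardless of whether they completed the entire study". It also plans an adjusted model with BMI, age, comorbidities, operator experience and the stratification factor.

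Withdrawal criteria says something different. It removes from the effectiveness analyses the outcomes of patients who are lost, refuse follow-up, withdraw, are judged unsuitable by the investigator, could not be given the intervention, or have no recorded data.

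Sample-size calculation {14} allows for 10% loss to follow-up and states that "the estimated non-inferiority margin is an absolute difference of 10% for the primary outcome measure".

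**The concern.** A missing-data indicator is a device for covariates. Used for a baseline variable in the adjusted model, it does little harm to a randomised comparison. It cannot fill in a missing binary outcome. A patient without an outcome drops out of the chi-square test and the generalised linear model, whatever indicator is coded.

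For outcomes, the rule that actually operates is therefore the exclusion under Withdrawal criteria. Several of its grounds can arise during the procedure and depend on staff judgement. Criteria for discontinuation {11b} lets the attending anaesthesiologist end participation for medical reasons, adverse reactions included. Who will be blinded {17a} says that the interventionists know the allocation and assess the outcomes. Exclusion could therefore depend on both the arm and how the patient is doing.

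The damaging case for non-inferiority is that the remimazolam patients left out did worse than those analysed. None of the listed analyses addresses it. The per-protocol set drops the same patients, and the broadened endpoint changes only what counts as success. The imputation is aimed at the indicators and, as ordinarily done, assumes that missing patients resemble similar observed ones.

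**Working it through.** **Inputs.** From Sample-size calculation {14}: propofol success 79%, margin 10 points, one-sided α 0.025, power 0.80, 10% loss, 288 per group. Assumptions: the true rate is equal in both arms (this reproduces the stated N), and non-inferiority is read from the lower limit of an unpooled Wald 95% interval for remimazolam minus propofol.

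**The plan's own figure.** n per arm = (1.960 + 0.842)² × 2 × 0.79 × 0.21 / 0.10² = 7.849 × 0.3318 / 0.01 = 260.4, so 261 per arm and 522 in total, as stated. Then 261 × 1.1 = 287.1, rounded up to 288 per arm and 576 in total, as stated. With 259 per arm observed, power is 79.8%. Lost precision is therefore not the problem.

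**Closed form.** Let m be the share missing per arm and d the shortfall in success among missing remimazolam patients, with missing propofol patients kept at 79%:

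lower limit = −m·d − 1.96 × √[2 × 0.79 × 0.21 / (288(1 − m))]

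- m = 0.10, d = 0: −1.96 × √(0.3318/259.2) = −0.070.
- m = 0.10, d = 0.30 (49% success): −0.030 − 0.070 = −0.100, so the margin is reached.
- m = 0.10, d = 0.79 (all fail): −0.079 − 0.070 = −0.149.
- m = 0.05: −0.068 at d = 0. The limit crosses −0.10 at d ≈ (0.100 − 0.068)/0.05 ≈ 0.63, or about 16% success.

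**Whole-patient counts.** With 29 missing per arm, 259 are observed and 205 succeed (79.2%) in each arm. Complete cases give a lower limit of −7.0 points. Counting every missing patient in both arms as a failure gives −7.4. With missing propofol patients at 79%, the limit passes −10 when success among missing remimazolam patients is about 47%: the difference is −3.2 and the limit −10.03. The 47% and 49% differ because this version treats filled-in values as observed, which narrows the interval slightly.

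**Lower limit (points) if all missing remimazolam patients fail:**

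| Missing per arm | Missing propofol at 79% | Missing propofol all succeed (extreme case) |
|---|---|---|
| 1% (3) | −7.5 | −7.7 |
| 2% (6) | −8.4 | −8.8 |
| 5% (14) | −10.7 | −11.7 |
| 10% (29) | −15.0 | −17.0 |

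**Effect on the error rate.** Suppose the truth sits on the margin (79% against 69%), those lost on remimazolam are all failures, and propofol losses are random. At 10% lost, observed remimazolam success is 0.69/0.90 = 0.767. The standard error is √[(0.767 × 0.233 + 0.79 × 0.21)/259.2] = 0.0365. The probability of declaring non-inferiority is Φ[(0.767 − 0.79 + 0.10)/0.0365 − 1.96] ≈ 56%, against a nominal 2.5%. At 5% lost it is about 17%, and at 2% about 6%. If failures are lost equally in both arms at 10%, it is about 1%. The harm comes from imbalance between arms, not from loss as such.

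**The case against.** The strongest objection is that the sentence on indicators never mentions the outcome. Its natural target is the covariates of the adjusted model, where the method is tolerable. This stands. A reader might infer that the plan codes missing successes and failures with indicators, but the article does not say so. What remains is that the sentence leaves outcomes to the withdrawal rule.

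Second, the 10% is a planning allowance for loss to follow-up, whereas every component of the primary outcome is observed in the same session. A missed telephone call the next day loses no primary data, an interruption for inadequate sedation is itself a recorded failure, and section {18b} commits to capturing outcomes in those who discontinue. This also largely stands: outcomes never observed may be few. It is not a full answer, because Withdrawal criteria, read literally, discards the outcome of a patient lost to follow-up even when it was observed.

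Third, tipping-point detail is usually left to an SAP, and none is at hand. Its absence alone would be no finding. The point rests on a stated method that cannot serve outcomes and on a stated exclusion that contradicts the stated population.

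Two further readings go too far. A reader might say that 10% loss threatens a shift as large as the whole margin. That needs every missing remimazolam patient to fail and every missing propofol patient to succeed (a shift of 29/288 = 10.1 points). A reader might also call the trial open-label, but patients are blinded, and the concern lies with staff. The Discussion says that outcome evaluators are blinded, contrary to {17a}. On either account the anaesthetist giving the drug is not.

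**Conclusion.** The point holds in this limited form. The stated missing-data method can serve only baseline covariates. Outcomes are governed by an exclusion rule that conflicts with the all-randomised ITT, and no listed analysis shows whether the verdict survives informative exclusion.

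The size depends on how many outcomes are missing or excluded, which the article does not settle. At 1–2% per arm the conclusion cannot flip under the assumed rates. At 5% it flips only if missing remimazolam patients do very badly. At 10% a shortfall of about 30 points is enough. These figures assume 79% observed success in both arms and equal missingness; a better or worse observed result would move the tipping point. This is a cheap and worthwhile improvement, not evidence that the trial's result will be wrong.

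**What to change.** 1. State that indicator variables are used only for missing baseline covariates.
2. Reconcile Withdrawal criteria with Efficacy evaluation {20a}, so that every randomised patient is in the primary ITT analysis and outcomes already observed are kept.
3. Impute a missing primary outcome by multiple imputation within arm, using the stratification factor and baseline variables.
4. Replace the present check with a tipping-point table: lower imputed remimazolam success stepwise, leave propofol at missing-at-random, and report the shift at which the lower limit crosses −10 points. Show the number missing or excluded, with reasons, by arm.

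The cost is some rewording and one extra table. The conclusion may look less favourable if outcomes are in fact missing.
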